#### Data Analysis

Analyses will be conducted using SAS (SAS Institute Inc) [32]. We will screen univariate distributions for normality and influential outliers and confirm that the randomization process balanced demographic characteristics between groups. We will also document the number of participants who are lost in each group, the reasons for the loss, and unintended crossovers. This information will influence the design of a future trial, including the frequency and mode of communication with clinicians and participants. The effect of the D-CHAT on care partner preparedness will be estimated as the difference in mean change from baseline to study completion between groups. The 95% CI will be calculated using a *t* distribution. Cohen *d* effect size will be calculated as the effect of the D-CHAT divided by the pooled standard deviation. This will give us a sense of the magnitude of the effect in terms of SDs. If normality assumptions in the raw data are not met and a simple transformation of the data (logarithmic or square root) does not sufficiently normalize the distribution, then we will use a nonparametric equivalent methodology [33]. If greater than 10% of the participants are noncompliant with their group assignment, then a per-protocol sensitivity analysis will be conducted to assess how influential the noncompliance was on the results of the study. Noncompliance is based on whether the group assignment was followed.

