#### Baseline Visit

The baseline visit will be completed in a designated room in the hospital to limit distractions. After completing consent, participants will complete descriptive measures and the primary clinical outcome measure (see Table 2). All measures will be administered by a trained, blind assessor. Immediately after these procedures, participants will be randomized to either the intervention or control group, and the clinical team will be notified of the assignment. These efforts will minimize bias and increase internal validity [28].

**Table 2 table2:** Measures.

Study measures		Instrument	Collection method	Time points	
				1^a^	2^b^

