#### Measures

Participants will be assessed on the measures listed in Table 2. Participants will be compensated US $25 after each time point is completed. Baseline measures will be collected in person at the hospital, and follow-up assessments will be administered via phone by a study team member. The primary clinical outcome we will measure is a change in care partner preparedness. The Preparedness for Caregiving Scale [30] is a self-rated measure that consists of 8 items that ask care partners how well prepared they believe they are for multiple domains of caregiving. Preparedness is defined as perceived readiness for multiple domains of the caregiving role, such as providing physical care, providing emotional support, setting up in-home support services, and dealing with the stress of caregiving. Responses are rated on a 5-point scale, with scores ranging from 0 (not at all prepared) to 4 (very well prepared). The scale is scored by calculating the mean of all items answered with a score range of 0 to 4. The higher the score, the more prepared the care partner feels for caregiving. The items have an internal consistency rating of 0.88 to 0.93. We will also collect secondary outcome measures, including satisfaction of care, caregiving burden, and depression, using standardized measures.

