#### Sample Size Justification

An estimated sample size of 128 will be recruited for the main trial based on the 95% CI width around the effect of the D-CHAT on care partner preparedness as measured by the Preparedness for Caregiving Scale [31]. Since this is a novel tool that will be adapted as part of phase 1, the variability of the response is unknown, and therefore justification is based on general terms of SD. With 64 subjects in both groups, the 95% CI width of the estimated effect will be 0.35 × SD. We expect to see a medium effect size (Cohen *d*=0.5). With this 95% CI width and expected effect size, we will have a sufficiently narrow CI of the true effect size to apply toward the planning of the future efficacy trial. If there was a ≈12% loss to follow-up such that 56 in each group have follow-up data, the 95% CI width would only increase to 0.375 × SD.

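### The primary effect is an unadjusted difference in change scores; adjusting for the baseline preparedness score already collected would probably narrow the confidence interval, by about 2% to 19% for assumed correlations of 0.9 down to 0.3

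*Protocol article*

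**What the plan says.** The Measures section defines the outcome: "The primary clinical outcome we will measure is a change in care partner preparedness". The Data Analysis section then fixes the estimator. The effect "will be estimated as the difference in mean change from baseline to study completion between groups", and "The 95% CI will be calculated using a" *t* distribution. Cohen d is that effect divided by a pooled SD; which SD is not stated. Baseline adjustment appears nowhere in the article.

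The Baseline Visit section says that after consent "participants will complete descriptive measures and the primary clinical outcome measure", and then: "Immediately after these procedures, participants will be randomized to either the intervention or control group". Table 2 lists preparedness, burden and depression at both time points, and satisfaction with care at follow-up only.

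The Sample Size Justification rests on interval width: "With 64 subjects in both groups, the 95% CI width of the estimated effect will be 0.35 × SD". With about "12% loss to follow-up such that 56 in each group have follow-up data", "the 95% CI width would only increase to 0.375 × SD".

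**The concern.** Subtracting the baseline score fixes its coefficient at 1, whatever the data show. If follow-up preparedness regresses on baseline with a slope other than 1, the change score carries variance that a fitted slope would remove. Both estimators target the same mean difference, because randomization makes the baseline means equal in expectation, and baseline is a legitimate covariate because it is recorded before allocation.

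In many pilots this would be a matter of taste. Here the 128 participants are justified by the width of the interval around this effect, and that interval is meant to inform the design of an efficacy trial. The choice of estimator therefore bears directly on the quantity the trial was sized to deliver.

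**Working it through.** **Inputs from the article.** 64 per group, or 56 per group after loss to follow-up; two-sided 95% CI from a t distribution; stated precision 0.35 × SD and 0.375 × SD. **Assumed, because the article gives neither:** the baseline to follow-up correlation ρ, taken as 0.3, 0.5, 0.7 and 0.9; and equal SDs at the two time points.

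**1. The plan's own figures.** Half-width = t(0.975, 2n−2) × SD × √(2/n).
- n = 64: 1.979 × √(2/64) = 1.979 × 0.1768 = 0.350 SD.
- n = 56: 1.982 × √(2/56) = 1.982 × 0.1890 = 0.375 SD.

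Both figures reproduce, as half-widths. The full widths are 0.700 and 0.749 SD. That labelling is a separate matter.

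**2. Variance of the two estimators.** Let β be the slope of follow-up on baseline. Per participant, the change score has variance σ²(follow-up) × (1−ρ²) + (β−1)² × σ²(baseline). Adjustment removes the second term, which is zero only if β = 1. With equal SDs, β = ρ, so:
- change: (1−ρ²) + (1−ρ)² = 2(1−ρ), in units of SD²
- adjusted: 1−ρ²
- ratio of variances: (1+ρ)/2
- ratio of interval widths: √((1+ρ)/2) = 0.806, 0.866, 0.922, 0.975 for the four values of ρ

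**3. Finite-sample half-widths.** The adjusted model uses t with 2n−3 degrees of freedom and the factor √(1 + 1/(2n−4)). At ρ = 0.5 and n = 64:
- change: 0.350 × √(2 × 0.5) = 0.350
- adjusted: 1.979 × 0.1768 × √0.75 × √(1 + 1/124) = 0.304

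95% CI half-widths in raw-score SD units:

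| ρ | 64/arm: change | 64/arm: adjusted | Narrower by | 56/arm: change | 56/arm: adjusted |
|---|---|---|---|---|---|
| 0.3 | 0.414 | 0.335 | 19% | 0.443 | 0.359 |
| 0.5 | 0.350 | 0.304 | 13% | 0.375 | 0.326 |
| 0.7 | 0.271 | 0.251 | 7% | 0.290 | 0.269 |
| 0.9 | 0.157 | 0.153 | 2% | 0.168 | 0.164 |

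**4. The same result in the other unit.** If the article's SD is the SD of change, the planned half-width is 0.350 at every ρ, and adjustment gives 0.283, 0.304, 0.324 and 0.342 at 64 per arm.

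**5. Simulation check.** With 56 per arm, a true effect of 0.5 SD and 8,000 trials per ρ, both estimators centred on 0.50. Mean half-widths, change versus adjusted, were 0.442 vs 0.358, 0.374 vs 0.325, 0.290 vs 0.269 and 0.167 vs 0.163. The adjusted interval was the narrower one in 100%, 100%, 99.4% and 83% of trials.

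**The case against.** The strongest reply is that nothing here is wrong. Outcome definition, estimator and precision figures fit together. The difference in mean change is unbiased under randomization and its t interval is valid. If the SD in the sample size section is the SD of change, the planned analysis delivers the half-width of 0.35 on which the trial was sized. All of this stands.

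The gain also depends on an unknown. The two assessments are about one hospital stay apart (within 24 hours of admission and within 72 hours of discharge), so a high correlation cannot be excluded, and at 0.9 the gain is only 2%. This stands, and it is why the range runs to 0.9. The advantage is a large-sample result: the lost degree of freedom cancels it at a correlation of about 0.98 or more, and below that an individual trial can still give a slightly wider adjusted interval.

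A reader might infer that chance baseline imbalance makes the planned estimate biased, as a second harm. The article does not support that. With equal SDs, a baseline difference of one standard error, √(2/64) = 0.177 SD, shifts the change-score estimate by (1−ρ) × 0.177: 0.124, 0.088, 0.053 or 0.018 SD for the four correlations. Over repeated randomizations this averages to zero and is already in the variance of the change score. It is largely the same efficiency loss seen from another side.

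Finally, Cohen d and the nonparametric fallback are both tied to the present estimator, so a change of model reaches further than one sentence. That is fair, and the fix allows for it.

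**Conclusion.** The point holds as a low-cost gain in precision. An analysis plan not shown here would not remove it, because the article itself names the estimator. At 64 per arm, baseline adjustment narrows the 95% CI by about 19%, 13%, 7% or 2% at correlations of 0.3, 0.5, 0.7 or 0.9. In terms of variance, that is what the planned analysis would need 64 × 2/(1+ρ) = 98, 85, 75 or 67 per arm to achieve.

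These sizes rest on equal SDs at both time points and on assumed correlations. With unequal SDs the gain depends on how far the slope lies from 1.

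A reader might go further and conclude that the pilot will miss its stated precision. That would follow only if the SD in the sample size section is the raw-score SD and the correlation is below 0.5. The article says neither.

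**What to change.** In the Data Analysis section, replace the estimator sentence with wording such as: *The D-CHAT effect is the adjusted between-group difference in follow-up Preparedness for Caregiving score, from a linear model with group and baseline score, reported with a t-based 95% CI. Mean change per group is given descriptively.* The outcome definition in Measures can stay, since regressing change on group and baseline gives the identical group coefficient.

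Three matching edits are needed:
- State which SD standardizes Cohen d, for example the pooled raw-score SD and not the residual SD of the adjusted model, which would give a different d.
- Use that same SD in the Sample Size Justification. In raw-score SD units, the adjusted half-width at zero correlation is 0.351 with 64 per arm and 0.376 with 56, and it is smaller at any positive correlation shown above. The present figures can therefore stay as approximate upper values.
- Word the normality check and nonparametric fallback to suit the model.

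Apply the same model to burden and depression, which Table 2 also lists at baseline. Satisfaction with care has no baseline.

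The cost is a few sentences and one residual degree of freedom, with no new data or participants.

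### The normality fallback names transformations that are undefined for negative changes, and it does not commit to keeping the mean difference, its 95% CI and Cohen d

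*Protocol article*

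**What the plan says.** The Measures section defines the outcome: "The primary clinical outcome we will measure is a change in care partner preparedness". It also fixes the scale: "The scale is scored by calculating the mean of all items answered with a score range of 0 to 4". A change score can therefore lie anywhere from -4 to +4, and a raw score of 0 is attainable.

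The Phase 2 Data Analysis section says that the D-CHAT effect will be "estimated as the difference in mean change from baseline to study completion between groups". It adds "The 95% CI will be calculated using a *t* distribution", and for Cohen d that the "effect size will be calculated as the effect of the D-CHAT divided by the pooled standard deviation".

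The same section then sets the fallback. It opens "If normality assumptions in the raw data are not met and a simple transformation of the data (logarithmic or square root" and continues that, where this "does not sufficiently normalize the distribution, then we will use a nonparametric equivalent methodology". The article gives no shift constant or reflection. It does not say whether scores or changes are transformed, does not name the nonparametric method, and does not say whether the mean difference and Cohen d are still reported once the fallback applies.

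The Abstract and the Design section give the pilot's aims as feasibility and the size of the effect. The Sample Size Justification says the interval will be used to plan the efficacy trial.

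**The concern.** The article fixes a data-triggered change to the primary analysis, and the fallback does not fit the outcome.

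- **The transformations do not suit change scores.** Log needs positive values and square root needs non-negative values. Change from baseline meets neither condition.
- **Transforming the raw scores changes the quantity.** The between-group contrast would be in log or root units, where an equal gain in points counts differently at different baselines. Without reflection, both transformations also make left skew worse.
- **The output is not protected.** The pilot is meant to deliver an effect in preparedness points and in SD units, with an interval. Under the fallback, the plan does not promise any of these.

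At stake is whether the result can be set against the expected d = 0.5 and the precision stated in SD units, and so whether it can serve the next trial's sample size calculation.

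**Working it through.** **1. The plan's own precision figure.** Inputs from the Sample Size Justification: 64 per group, or 56 per group after about 12% loss. The half-width of the t interval is t(0.975, 2n-2) × √(2/n) × SD.
- n = 64: 1.979 × √(2/64) = 0.350 SD
- n = 56: 1.982 × √(2/56) = 0.375 SD

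Both stated figures reproduce, as half-widths. (The article calls them widths, which is a separate matter.) They refer to a mean difference in SD units, and that is the quantity the fallback leaves unprotected.

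**2. How many changes would be negative.** Input from the document: d = 0.5. The article says the variability is unknown and gives no control-group change. Assumptions: change is normal, the SD in d is that of change, and mean control change is m SD, with m from 0 to 1.0. The share below zero is Φ(-m) in controls and Φ(-(m + 0.5)) in the D-CHAT arm.

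| m (SD) | Control | D-CHAT | Average | Expected count of 128 |
|---|---|---|---|---|
| 0 | 0.500 | 0.309 | 0.404 | 64 × 0.809 ≈ 52 |
| 0.25 | 0.401 | 0.227 | 0.314 | 64 × 0.628 ≈ 40 |
| 0.5 | 0.309 | 0.159 | 0.234 | 64 × 0.467 ≈ 30 |
| 1.0 | 0.159 | 0.067 | 0.113 | 64 × 0.225 ≈ 14 |

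The chance that no participant has a negative change is (1 - control share)^64 × (1 - D-CHAT share)^64. It is below 2 × 10⁻⁷ in every row. This last step uses only the shares, not the normal shape, and a single negative change is enough to make the unshifted transformation undefined for the data set.

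**3. The same check on the bounded scale.** A simulation used scores in steps of 1/8, clipped to 0 to 4, with 64 per arm. Assumptions: baseline mean 2.2, SD 0.8, effect 0.4 points, control change 0, 0.2 or 0.4 points, and baseline to follow-up correlation 0.5 or 0.7. Between 15% and 37% of changes were below zero, and between 21% and 43% were at or below zero.

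**4. Transforming the 0 to 4 scores instead.** Square root is always defined. Log fails at a score of 0. In the same simulation, 39% to 53% of trials had at least one such score at baseline or follow-up. The contrast also changes meaning. For a 0.5-point gain:
- from baseline 0.5: √1.0 - √0.5 = 0.29
- from baseline 3.5: √4.0 - √3.5 = 0.13

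The same gain in points counts more than twice as much at the low end.

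**5. The nonparametric step.** A rank-sum test and a Hodges-Lehmann shift could be computed on change in every simulated trial. The shift was close to the mean difference, for example 0.382 against 0.380. It is in preparedness points, but it does not give Cohen d.

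**The case against.** There is a fair case for reading the rule more kindly.

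- **The trigger may mean the collected scores.** The rule speaks of raw data, which can be the 0 to 4 scores. Square root then works throughout, and log fails only at 0. This reading is open. It removes most of the undefined values but not the change of scale.
- **The fallback as a whole can be carried out.** A reader might infer that none of it can be computed on change scores. That is wrong: the nonparametric step can.
- **Nobody need be excluded.** A reader might infer that participants who did not improve would be dropped because their values are undefined. The article does not say so. A transformation that cannot be applied leads naturally to the next step, with everyone retained.
- **The method is not stated to be rank-based.** The wording is only "then we will use a nonparametric equivalent methodology", with a reference that is not available here. A bootstrap interval for the mean difference would also qualify. An analysis plan could name the method and a shift constant.
- **Replacement is not stated.** The mean difference and Cohen d are promised without condition, and the fallback sentence does not withdraw them.
- **The 11% to 40% range assumes normal change.** If change is what is checked, that is the case in which the fallback would not be triggered.

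All of this stands, and it narrows the point. What remains is that the two named transformations do not suit the stated outcome, and that the article leaves open whether its main effect-size output survives the switch.

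**Conclusion.** The point holds in limited form. Applied to change without a shift, log and square root are undefined for negative values, and log also for zero. Such values are practically certain. The range of 11% to 40% of participants shows the order of magnitude and rests on the assumptions in step 2; it does not describe the data that would trigger the rule. Applied to the raw scores, the transformations move the contrast off the preparedness scale. The nonparametric step is feasible, but the plan does not commit to reporting the mean difference, its 95% CI and Cohen d beside it.

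The documents do not support the stronger readings that the whole fallback is incomputable, that participants would be excluded, or that the mean difference is certain to be discarded.

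The switch also has little to offer. A t interval depends on the sampling distribution of the mean difference. With 56 to 64 per arm on a bounded scale, that is usually close to normal even when individual values are not. This is a general property of means and was not calculated here.

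**What to change.** In the Phase 2 Data Analysis section:

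1. Remove the log and square-root step.
2. State that the between-group difference in mean change on the 0 to 4 scale, its 95% CI and Cohen d will always be reported, whatever the normality check shows.
3. If the distribution is markedly non-normal, give a bootstrap or robust CI for that same estimate.
4. Label any rank-based analysis as a sensitivity analysis.

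The cost is one or two sentences of wording and very little programming in SAS. The sample size, data collection and the planned primary estimate do not change.

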## Results

We anticipate this study to take approximately 60 months to complete, from study start-up procedures to dissemination. The 2 phases will take place between December 1, 2022, and November 30, 2027. We expect the following results:

Phase 1—formative research: Results will provide a converged-upon, ready-for-feasibility testing, D-CHAT, to guide clinicians’ identification and preparation of care partners in hospital care of people living with dementia. The D-CHAT will include caregiving domains unique to dementia caregiving and discipline-specific treatment to meet the needs of care partners.Phase 2—main trial: A total of 128 eligible care partners of hospitalized people living with dementia will be randomized into either the D-CHAT plus usual care or usual care-only groups. Descriptive and feasibility characteristics for delivering the D-CHAT will be collected. We expect that care partners who receive the D-CHAT will demonstrate larger improvements in caregiving preparedness than those in the usual care group.

Findings from both studies will be disseminated following best practices throughout the conduct of this research. The study is registered at ClinicalTrials.gov in accordance with current National Institutes of Health (NIH) policies and federal regulations (NCT05592366). Results will be posted to ClinicalTrials.gov within 12 months of study completion. Across all stages of the research, we will publish peer-reviewed papers and present our findings at conferences attended by researchers and clinicians in diverse and relevant fields. We will also share the results of this study directly with relevant and interested parties by developing infographics. These will be distributed through dementia caregiving networks and established partnerships.

## Discussion

Lack of caregiving preparedness is prominent and persistent among care partners of people living with dementia and is associated with increased risk for adverse clinical outcomes for people living with dementia [2,3] and increased levels of burden, depression, and morbidity for care partners. While clinical decision-support tools offer a valuable resource for addressing this gap in practice, no tool exists to guide the systematic identification and preparation of care partners for hospitalized people living with dementia [16].

We will involve a broad range of individuals in the participatory co-design process to create a converged-upon, ready-for-feasibility testing D-CHAT. Moreover, we will use the novel clinical decision-support tool to facilitate the timely identification and preparation of care partners during hospital-based care delivery processes. This work will help bridge the gap between recommendations or policy and practice by providing clinicians with guidance on how to identify and better prepare care partners for hospitalized people living with dementia.

The control group will be randomized to usual care delivered by medical and surgical acute care teams at 1 large academic medical system. While we realize that these teams could prepare care partners for people living with dementia without intervention, we consider the D-CHAT to be more of an individualized care approach that systematically and comprehensively identifies and prepares care partners to fulfill their caregiving responsibilities after the patient discharges from the hospital. The intervention may be seen as burdensome by some clinicians. Our protocol has plans in place to train clinicians on the D-CHAT to ease workflow demands prior to beginning the main trial phase. We are also aware of the potential for measurement bias in the study design (ie, care partners may underreport caregiving needs and preparedness). Therefore, this issue will be discussed during the formative research phase and brought up in the co-design process to develop the best approaches to minimize these potential concerns. We also recognize that hospitals may enforce visiting restrictions at any given point because of the COVID-19 pandemic. For this reason, we have collaborated with research directors and clinical nurse scientists at the academic medical system to identify ways to adapt our data collection and communication approach so that we minimize the potential risks to both hospitalized people living with dementia and their care partners.

Engaging diverse and interested parties to adapt the standardized CHAT for hospital-based dementia care will expand its potential reach. Further, findings from this pilot randomized controlled trial will enable future efficacy trials to advance the refinement and implementation of the decision-support tool that can enhance caregiving preparedness and improve health outcomes after hospital discharge [34]. We anticipate that the resultant D-CHAT will provide clinicians with guidance on how to identify and better prepare care partners for hospitalized people living with dementia. In turn, care partners will feel equipped to fulfill caregiving roles for their family members or friends living with dementia.

